. Details of the resources consumed in each arm (averages and dispersion) and the average costs and efficiency per doctor will be calculated for each arm.

. A table will show the difference between the two groups in terms of costs and effectiveness, and the cost-effectiveness ratio will be calculated.

. As costs are not generally distributed according to a normal distribution, the incremental cost-effectiveness ratio and its confidence interval will be estimated using the non-parametric bootstrap method [49].

Finally, the probability that the use of antibioclic associated with a specific DAM visit is cost-effective compared with *a standard DAM visit* will be calculated for different values of willingness to pay for a reduction in antibiotics.

- - 1. ***STATISTICAL JUSTIFICATION FOR THE NUMBER OF INCLUSIONS***

After preliminary work to explore feasibility with the Assurance Maladie teams, the number of eligible doctors was estimated at 2,400 GPs who saw more than 100 different patients in 2018. The average number of DDDs dispensed per doctor in 2018 was 7,671, with a standard deviation of 5,360. In 2018, the average number of DDDs dispensed per doctor was 7671, with a standard deviation of 5360. Due to cluster randomisation, an inflation factor must be applied to calculate the number of subjects. In a previous study in the Loire Atlantique and Vendée regions [47], the average number of GPs per practice was 1.9. We set an intra-class correlation coefficient of 0.05 [50].

With an alpha risk of 5% and power of 80%, we can then demonstrate a significant difference if we have at least an average difference of 450 DDD per doctor (over the 12 months following the DAM visit) between the arms being compared.

- 1. ***Expected degree of statistical significance***

The alpha risk is set at 5%.

- 1. ***Method for taking into account missing, unused or invalid data***

All analyses will be performed on an intention-to-treat (ITT) basis.

The volumes of systemic antibiotics dispensed attributed to doctors who ceased their activity (end of career, moving outside the region, death, etc.) during the study follow-up period will be replaced by multiple imputation. A sensitivity analysis of the per-protocol population will also be carried out, excluding these doctors, as well as those who did not receive a visit from the DAM, and those who were not computerised.

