For doctors who have not been visited by the DAMs, the start date of the data collection period will be allocated by drawing lots, and staggered over the 3 months (start date based on the visit dates available for the 3 randomisation arms).

- 1. ***Randomisation***

The Assurance Maladie will generate a list of GP practices that meet the inclusion criteria. It will then randomise the GP practices on a 1:1:1 basis. Doctors will be assigned to the randomisation arm to which their practice has been allocated.

1. **SAFETY / UNDESIRABLE EFFECT**

In the regulatory sense and within the meaning of the Jardé Law, this study does not constitute research involving human subjects. In the regulatory sense and within the meaning of the Jardé Law, this protocol does not involve any change in the usual management of patients, so any adverse events or effects observed will be unrelated to the study.

1. **MEDICO-ECONOMIC STUDY**

This section presents the objectives and methodology of the efficiency analysis, based on a cost-effectiveness analysis. The economic evaluation methodology follows the 2011 recommendations of the French National Authority for Health [49].

- 1. ***Objective, perspective and time horizon of the cost-effectiveness analysis***

The study involves a cost-effectiveness analysis comparing the delivery of antibiotics over a 12-month period in current practice, compared with two alternative strategies

i) an intervention carried out by the Délégués d'Assurance Maladie (Health Insurance Representatives) in general practices, combining a regular visit (with awareness-raising on antibiotic resistance, work on preconceived ideas, feedback on practices) and a demonstration of the use of Antibioclic,

1. an intervention carried out in the same way by the Délégués d'Assurance Maladie, but without Antibioclic being demonstrated.

This analysis will be carried out from the point of view of the Assurance Maladie Obligatoire over a 12-month period.

Costs will be estimated on the basis of information retrieved from the SNDS databases extracted by the Assurance Maladie in Pays de la Loire. The resources consumed will be valued at Assurance Maladie prices for drugs.

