Given that two strategies will be compared with current practice, it may be necessary to estimate several incremental cost-effectiveness ratios (ICERs). A dominance analysis will be carried out to check whether certain interventions are dominated, i.e. more costly and less effective than another intervention. The average incremental cost-effectiveness ratio will be presented, together with its 95% confidence interval.

Univariate and multivariate sensitivity analyses will be carried out to check the robustness of the results to changes in assumptions about certain study parameters.

- 1. ***HEALTHCARE CONSUMPTION AND VALUATION***

The costs of the three strategies compared will be estimated in three stages [48]:

. collection of resources consumed,

. the unit monetary value of resources,

. estimated total costs.

Deliveries and costs of systemic antibiotics will be estimated using information retrieved from SNDS databases extracted by the Assurance Maladie in Pays de la Loire. The resources consumed will be valued at Assurance Maladie prices for drugs.

The resources used as part of the study will include :

. the costs associated with preparing and holding the training course,

. training time for DAMs,

. the development of communication material,

- the time it takes to create a digital visual aid,

- time for role-playing,

- the time it takes to write a sales pitch,

- time to rewrite the memo cards.

. time doctors

. the average duration of use of Antibioclic by doctors

We will take into account antibiotic dispensing based on the doctor's prescription and the monitoring of activity over a 12-month period. The costs will be calculated using Assurance Maladie tariffs.

This will be done by combining the results of the two previous stages. Given the 12-month time horizon, the costs will not be discounted. We will present the average costs per patient in each arm.

- 1. ***Efficiency data***

Effectiveness will be measured by the ratio between deliveries of defined daily doses (DDD) observed in the Assurance Maladie databases and the WHO defined daily doses between the different scenarios in the analysis [46-47].

We will look at defined daily doses (DDD) of all types of systemic antibiotics for all patients per 100 consultations [51]. To do this, we will stratify by specific antibiotic types (ie, tetracyclines, quinolones, β. lactamine/penicillin, other β. lactamine, other antibacterials, unspecified, etc.).

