Finally, we will stratify the patient populations into 4 classes: young children (0 to 6 years), children over 6 years and adolescents (7 to 17 years), young adults (18 to 65 years) and finally the elderly (over 65 years) and between men and women.

- 1. ***Presentation of results***

In accordance with ISPOR recommendations on economic evaluation [52,53], we will present the results of the medico-economic analysis as follows:

. average antibiotic costs per arm and the difference in costs with its 95% confidence interval

. Mean efficacy per arm and the difference in efficacy with its 95% confidence interval

As costs are not generally distributed according to a normal distribution, the incremental cost-effectiveness ratio and its 95% confidence interval will be estimated using the non-parametric bootstrap technique.

Finally, sensitivity analyses will be carried out to study the robustness of the results on certain key parameters of the study.

1. **ADMINISTRATIVE AND REGULATORY ASPECTS**
   1. ***Right of access to source data and documents***

The data extracted as part of the study will not be nominative, whether it concerns physician data or patient data. They will only be transmitted to the sponsor or any person duly authorised by the sponsor, and, where applicable, to the authorised health authorities, under conditions which guarantee their confidentiality (see 7.1.COLLECTION AND PROCESSING OF STUDY DATA).

There is no provision for access to source documents. This means that there will be no export of nominative data outside the usual health insurance databases.

The data collected during the trial will be processed electronically, in compliance with CNIL requirements.

- 1. ***Computerised data and submission to the CNIL***

Data processing will be recorded in the Nantes University Hospital's RGPD register.

The data collected during the study will be kept in a computer file that complies with the amended French Data Protection Act of 6 January 1978, Law No. 2018-493 of 20 June 2018 on the protection of personal data and Regulation (EU) 2016/679 of the European Parliament and of the Council of 27 April 2016 on the protection of individuals with regard to the processing of personal data and on the free movement of such data (RGPD).

The protocol falls within the scope of the MR004 Reference Methodology to which Nantes University Hospital complies.

- 1. ***Inspection / Audit***

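### Sections 9.1 and 9.4 of the protocol conflict with 9.2 on which costs enter the economic result, and no section names the cost numerator of the ICER or the dominance check

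*Protocol*

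**What the plan says.** Four places in the protocol describe the cost side of the economic evaluation.

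- **Section 9.4 (Presentation of results)** lists two result lines before the bootstrap ICER. The cost line is "average antibiotic costs per arm and the difference in costs with its 95% confidence interval"; the other is the corresponding line for efficacy. It has no line for programme cost or total cost.
- **Section 9.1 (Objective, perspective and time horizon)** takes costs from the SNDS extraction and continues: "The resources consumed will be valued at Assurance Maladie prices for drugs". It also plans a dominance analysis, in which a strategy is "dominated, i.e. more costly and less effective than another intervention".
- **Section 9.2 (Healthcare consumption and valuation)** builds the costs of the three strategies in three stages, the last being "estimated total costs". The resources include "the costs associated with preparing and holding the training course", "training time for DAMs", development of the communication material, doctors' time and time spent on Antibioclic. On presentation it says: "We will present the average costs per patient in each arm".
- **The statistics section (7.2, secondary endpoints, item 5)** says: "Details of the resources consumed in each arm (averages and dispersion) and the average costs and efficiency per doctor will be calculated for each arm". It then plans a table of cost and effectiveness differences with the ratio, and does not say which costs are meant.

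**The concern.** Two analysts could follow this protocol faithfully and report different cost differences. One who starts from 9.1 and 9.4 prices the dispensed antibiotics and stops. One who starts from 9.2 adds the resources spent on training, materials and time. An analysis plan would normally refine a definition of cost, but here the protocol itself gives two.

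The choice matters because effectiveness is also built from DDD (section 9.3). If the cost difference is antibiotic cost alone, both axes of the cost-effectiveness plane derive from the same dispensing data. The dominance check and the willingness-to-pay probability then say little about whether the programme pays for itself. The ICER is a named secondary criterion, and section 3 lists reduced cost among the expected benefits, so readers will look to this result for the answer.

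**Working it through.** The protocol states no cost figure, so there is none to reproduce. The check is a comparison of the passages, followed by an illustration of size.

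**1. The passages side by side**

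| Place | Costs covered | Unit of presentation |
|---|---|---|
| 9.1 | SNDS data, valued at drug prices | not stated |
| 9.2 | Total costs, including programme resources | per patient |
| 9.4 | Antibiotic costs | per arm, no denominator given |
| 7.2, item 5 | Average costs, scope not stated | per doctor |

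The ICER appears in 7.2, 9.1 and 9.4 and the dominance check in 9.1. None of these defines the cost numerator.

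**2. Inputs for the illustration**

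- DDD avoided per doctor: 450, the difference given in the sample size justification. It is used for scale only; nothing here depends on whether it is the right detectable difference.
- Mean DDD per doctor in 2018: 7,671 (same section).
- Price per DDD: not in the documents. Assumed range EUR 0.5 to 1.5.
- Incremental programme cost per doctor, ΔP: not in the documents. EUR 500 is assumed for one column.

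**3. Cost difference, intervention minus arm 3, at an unchanged mean price per DDD**

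- Antibiotic cost only: −(450 × price).
- Total cost: ΔP − (450 × price).
- Break-even: ΔP = 450 × price.

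| Assumed price per DDD (EUR) | Antibiotic-only difference (EUR per doctor) | Break-even ΔP (EUR per doctor) | Total difference if ΔP = 500 (EUR per doctor) |
|---|---|---|---|
| 0.5 | −225 | 225 | +275 |
| 1.0 | −450 | 450 | +50 |
| 1.5 | −675 | 675 | −175 |

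Omitting programme cost can therefore reverse the sign, but need not. With no effect on DDD and no change in price, the antibiotic-only difference is zero, while the total difference is ΔP.

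**4. How far a fall in DDD implies a saving**

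A fall of 450 from 7,671 is 450 / 7,671 = 5.9%, leaving 7,221 DDD. Antibiotic cost is unchanged if the mean price per DDD rises by 7,671 / 7,221 − 1 = 6.2%. A fall of this size is a saving only if the mean price rises by less than that.

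**The case against.** A reader might infer that the evaluation leaves programme costs out and that the interventions must therefore come out dominant. The documents do not support that, for these reasons.

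- Section 9.2 counts the programme resources and carries them into a total. Section 7.2 speaks of resources consumed and average costs without limiting either to antibiotics. No passage excludes programme costs or says that the ICER or dominance check uses antibiotic costs alone.
- The drug-price sentence of 9.1 recurs in 9.2 directly after a sentence on systemic antibiotics and before the separate list of programme resources. In that place it reads naturally as valuing the antibiotic component only.
- A fall in DDD is not automatically a saving. Both interventions aim to shift the choice of drug, so the mean price per DDD may move, and a rise of 6.2% would cancel the saving from 450 DDD. Cost and effect are also not identical: they differ by price weights and by the scaling per 100 consultations in 9.3.
- Arm 3 also receives a delegate's visit, on another theme. To the extent that visits cost the same, their cost cancels, and only the programme cost incremental to arm 3 counts.
- The break-even is not trivial. With about 800 doctors per arm, EUR 225 to 675 per doctor is EUR 180,000 to 540,000 per arm. The documents do not show that the programme costs this much.

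All of this stands, and it limits the point to an inconsistency. It does not remove it: 9.4 still labels its only cost line as antibiotic costs, 9.1 carries no restriction of drug prices to antibiotics, and the numerator remains unnamed. The layout of a cost table can be left to an analysis plan, but two competing definitions of cost in the protocol should be settled there.

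**Conclusion.** The inconsistency is real and worth correcting. Sections 9.1 and 9.4 point to antibiotic cost, section 9.2 points to total cost, and 7.2 does not decide between them. If 9.4 is followed as written, the payer receives a cost difference without the programme resources that the protocol itself lists. At a stable mean price per DDD, the arm with fewer DDD would then appear cheaper and more effective regardless of programme cost.

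The size cannot be fixed from the documents. For 450 DDD and an assumed EUR 0.5 to 1.5 per DDD, with an unchanged mean price, the sign of the cost difference changes only if incremental programme cost exceeds EUR 225 to 675 per doctor. Whether it does is unknown. The point concerns secondary objective 5 and does not touch the primary endpoint.

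**What to change.** - **Section 9.4:** replace the cost line with mean total cost per arm, defined as antibiotic cost plus the 9.2 programme resources incremental to arm 3. Show the two components separately, and give the difference in total cost with its 95% confidence interval.
- **Numerator:** name total cost as the cost used in the ICER, the bootstrap and the dominance check.
- **Section 9.1:** state that drug prices value only the antibiotic component.
- **Unit:** use one unit in 7.2, 9.2 and 9.4. Per doctor would match the statistical unit of the trial.

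The cost is wording only, since the programme resources are already listed in 9.2. The reported cost difference can become less favourable to the interventions.
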